### Study intervention

#### Standard rehabilitation

All patients will receive standard-of-care physiotherapy during hospitalization. Physiotherapy will commence on the day of surgery with mobilization using a walking aid (usually two crutches, rarely a walker), deep vein thrombosis prevention exercises, lower limb range of motion exercises, and an isometric strengthening program. Patients will be encouraged to perform exercises twice daily, with approximately 10 repetitions of every exercise, and walk as much as possible. Exercises will be performed in a supine position, on the healthy side, on the abdomen, sitting and standing (e.g., buttock squeezes, leg sliding motions, straight leg raises, bridges, postural exercises). Patients will be discharged based on a combination of compliance with the exercises, stability with a walking aid, independence with activities of daily living, and dry wounds. Patients in the CG will receive written instructions, a USB drive with videos of standard exercises, and a training diary at discharge.

#### Prescribed home-based strength and sensory-motor training

Before the patients are discharged, physiotherapists will teach patients in the IG special strength and sensory-motor exercises with exercise aids. The patients will also receive USB drives with special exercise videos, written exercise instructions, and a training diary to check performed exercises. The new training protocol includes exercises for improving hip stability and reducing local stresses on the hip prosthesis. In the training, we considered safety regarding hip and lumbar spine load, falls, and prosthesis luxation. Training will consist of hip muscle strengthening exercises (focusing on the abductors), hip and pelvic stabilization exercises, ankle and knee muscle strengthening exercises (for improved dissipation of impact forces and femoral inner rotation control), and trunk muscle strengthening exercises (for stabilization of the pelvis and lumbar spine and a reduction in local loads). We ensured the exercises are simple and easy to understand, the videos that are to be watched at home are easy to follow, and the training program does not require expensive equipment. In the first two postoperative weeks, the focus is on learning the proper exercise technique and developing a sense of loading. Patients will watch special instructional short videos with exercise descriptions. Each exercise will be demonstrated with easy and challenging options as well as oral and written instructions. We will use a revised Borg category-ratio scale (0 to 10 scale) for perceived exertion to monitor and guide exercise intensity [33]. In sets of fluent concentric repetitions of movements (10–12 repetitions per set), the rating of perceived exertion will be recorded for the last repetition. When holding an isometric position, the rating will be recorded for the end of the interval (with a lengthening of the interval to 30 s, until we can achieve desired perceived exertion at the end of the interval). In sets of isometric contractions, every repetition will be made with the maximal voluntary effort exerted for 6 s (2 s for force increments and 4 s for maintenance). The implementation of fluent concentric movements is intended to increase muscle mass and improve physical endurance, while maximal isometric contractions are used for improving the level of muscular activation [34]. Exercises with isometric trunk positions will be prepared with recommendations for isometric trunk stabilization training [35]. These concepts collectively allow for individual load adaption for every exercise regarding individual patient abilities and load progression in accordance with his or her progress in muscle strengthening training [34]. Each session consists of a warm-up with 2 options (5–7 min of toe walking on the same spot or step-ups on a 10-cm tall step), strength training for both legs (30–40 min; 11 exercises; 1–4 fluent concentric repetitions of the single-leg squat and lying side hip raise; 5–8 maximal isometric contractions of the sitting ball squeeze, seated elastic band hip abduction, and diagonal ball push into the opposite thigh; 9–11 holds in the isometric positions, side plank, and bridge), and stretching (standing hip flexor stretch, sitting forward bend stretch, standing lateral trunk stretch). Strength training will be performed twice weekly, with a minimum of 2 days of rest. Until the 5th postoperative week, perceived exertion will be increased on the Borg scale from 5 to 8, and then it will be increased to 9 until the assessment at 3 months. In the first 5 postoperative weeks, 2 sets of each exercise will be recommended, and after these 5 weeks, 3 sets will be recommended. Sensory-motor training will be added to strength training to increase muscular activation and rate of force development and will be practiced on the days without strength training [36]. Exercise for ankle stability will be performed with a one-dimensional wooden balance board in the frontal and sagittal plane [37]. At the beginning, patients will perform 6 sets for each leg and 12 sets after the 7th postoperative week. The intensity of the exercise will be increased according to patient abilities with changes in the stability of the balance board. For every exercise, severe pain will be a reason for training cessation and contact with the physiotherapist.

### Outcome measures

The primary outcome of the study is the efficacy of the chosen protocol, measured by physical tests. These comprise the 10 MW test, the 8-foot Up and Go (8UG) test, and isometric muscle strength. Secondary outcomes are the patient questionnaires, which will be used to draw conclusions about patient satisfaction and the feasibility of the protocols, and consistent recording of any adverse effects.

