**Methods/design:**

This study is a prospective multicenter randomized clinical trial to be conducted in the orthopedic departments of two Slovenian hospitals. In each hospital, 124 patients aged 60 or older with unilateral osteoarthritis, an ASA score between 1 and 3, a signed informed consent form, and no terminal illness disabling rehabilitation participation will be randomly assigned to the intervention or control group. THA with an anterior approach will be performed. All patients will receive current standard physiotherapy during hospitalization. Patients in the intervention group will also learn strength and sensory-motor training exercises. Upon discharge, all will receive USB drives with exercise videos, written exercise instructions, and a training diary. Physiotherapists will perform the assessments (physical tests and the maximal voluntary isometric contraction assessment), and patients will fill out outcome assessment questionnaires (the Harris Hip Score and 36-Item Short Form Health Survey) at baseline and 1, 3, and 12 months after surgery.

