### Objectives

The primary objective of our study is to evaluate the efficacy of an early postoperative home-based strength training protocol — to assess whether it can improve patient functional outcomes at 3 months and 1 year following surgery. The secondary objectives are the feasibility of the presented protocol for all elective THA patients and its safety.

Our study also aims to assess patient satisfaction with enhanced targeted physiotherapy and to prepare a new standardized rehabilitation protocol with videos that will be effective, safe, and accessible to all THA patients.

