## Methods/design

### Study design

The study is a multicenter randomized controlled trial comparing the effect of intensive early postoperative physiotherapy with the current standard of physiotherapy for patients undergoing elective THA for unilateral OA. General Hospital Novo mesto and Valdoltra Orthopedic Hospital are involved in the project, and the standard physiotherapy program for patients after THA is similar in both hospitals. All patients who will receive an anesthesiologist’s approval and will already be scheduled for surgery will be assessed for eligibility. An orthopedic surgeon will invite patients to participate and give oral and written explanations about the trial. Patients will be included in the study after signing a written informed consent form. After admission to the hospital, they will complete the routine preoperative outcome assessment questionnaires (Harris Hip Score (HHS) and 36-Item Short Form Health Survey (SF-36)) and have standard preoperative AP X-rays of both hips taken. Physiotherapists will perform the assessments: physical tests and an isometric muscle strength assessment. In both hospitals, the included patients will be randomized to either the intervention group (IG) or the control group (CG), and the surgeons and patients will be blinded to the randomization process. The procedure will be performed with the direct anterior approach only in the General Hospital Novo mesto by 1 surgeon and in the Valdoltra Orthopedic Hospital by 4 surgeons. Patients will be mobilized on the day of surgery. During the expected LOS of 2–5 days, all patients will receive current standard physiotherapy, oral analgesics, and cryotherapy. Patients in the IG will receive extra one-on-one training to learn strength and sensory-motor exercises. If the surgeon applies any limitations for a patient regarding rehabilitation after surgery, the patient will be excluded from the study. At discharge, patients in both groups will receive USB drives with exercise videos, written exercise instructions, and a training diary. Patients in the IG will also receive exercise aids for the strength and sensory-motor training. All patients will be followed up with regular phone calls concerning possible complications, completion of the training diary, and the clarity of the exercises. The patients will visit the hospital as usual after 1, 3, and 12 months following surgery. At each follow-up, the physiotherapists will perform assessments, and patients will fill out questionnaires. The patients will have a standard postoperative X-ray of the operated hip immediately after the surgery and AP X-rays of both hips after 1 year, so we will be able to compare measurements of the hip offsets of the operated and healthy hips and observe any changes regarding component position or osteolysis. At every follow-up, the surgeon and physiotherapist will ask the patient about any adverse effects or reasons for training cessation. The trial flowchart is displayed in Fig. 1.

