#### Maximal voluntary isometric contractions

We use a specially prepared measuring device with a dynamometer attached to stiff band metal chains, prepared similarly to those in Roussel et al. and Essendrop et al. [38, 39]. The ICC for a similar device, used by one of the senior authors for lumbar muscle strength assessment, is > 0.94. For the assessment of maximal isometric strength, a maximal voluntary isometric contraction for 6 s is used. The same procedure of obtaining a maximal voluntary contraction is used for every strength measure. Movement is assessed in 3 planes for the trunk (extension, left and right abduction) and operated hip (flexion, extension, and abduction), and movement is assessed in 2 planes for the contralateral hip (extension, abduction). All strength tests are performed in a neutral standing position, and the patient rotates on the measuring device so that the exerted force is always in the direction opposite of the dynamometer. Before the measurements, the height of pelvic support is set to the reference point of the iliac crest of each patient. Patients are verbally encouraged to generate maximal effort. The mean duration of the complete test is 20 min. We wrap the band around the trunk under the armpits for trunk tests and around the ankle for leg tests. We measure the height of pelvic support, maximal contraction force, and distance between the upper border of the support board and the middle point of the stiff band. All measurements are taken twice.

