## Discussion

We have had good experiences with the standard exercise protocol, so we anticipate that the majority of the patients from both groups will have better performance at 3 months and 1 year after surgery compared to at baseline. All patients should also have higher scores on patient satisfaction questionnaires at 3 months and 1 year after surgery than at baseline. We expect patients in the intervention group to achieve better results in physical tests and maximal voluntary isometric contraction measurements compared to patients in the control group. With respect to other studies, we predict the largest differences at the 3rd postoperative month. We would like to provide evidence that home-based strength and sensory-motor training is safe and easy to understand for the majority of patients and is applicable to all THA patients.

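### Isometric strength is part of the primary outcome although the primary objective is function, so a strength-only difference could be reported as primary efficacy

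*Protocol article*

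**What the plan says.** **Objective.** Under Objectives, the primary aim is efficacy, spelled out as "to assess whether it can improve patient functional outcomes at 3 months and 1 year following surgery".

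**Primary outcome.** Under Outcome measures: "The primary outcome of the study is the efficacy of the chosen protocol, measured by physical tests". The next sentence lists them: "These comprise the 10 MW test, the 8-foot Up and Go (8UG) test, and isometric muscle strength". The secondary outcomes named there are the questionnaires and adverse effects, so strength appears only as primary.

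**Strength measures.** The section on maximal voluntary isometric contractions lists three trunk directions, three for the operated hip and two for the other hip.

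**Sample size.** The calculation uses a gait-speed difference of 0.10 m/s and an SD of 0.28 m/s, and gives 124 per group. No strength difference is used.

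**Testing.** Data management and analysis applies P < 0.05, two-tailed, to all measures. No component is ranked above another, and no rule says which of them must succeed.

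**Terminology elsewhere.** Three places name strength beside physical tests, not within them: the abstract's methods ("physical tests and the maximal voluntary isometric contraction assessment"), Study design ("physical tests and an isometric muscle strength assessment") and the Discussion ("better results in physical tests and maximal voluntary isometric contraction measurements").

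**The concern.** The primary outcome contains something the primary objective does not ask about. The objective concerns function. Maximal force on a dynamometer is a measure of strength, and the article's Background itself names muscle strength and function as two things that training improves.

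Because strength is listed on equal terms with the two functional tests, and nothing says which component carries the claim, a trial in which strength improved while gait speed and 8UG did not could be reported as positive on its primary outcome. Readers would take that as evidence of better function.

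This is not mainly a matter of chance findings. A real strength effect would survive any adjustment for multiple testing and would still not answer the stated question.

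**Working it through.** **1. Reproduce the plan's figure.** Inputs from Sample size calculation: difference 0.10 m/s, SD 0.28 m/s, two-sided 5%, power 80%.

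n per group = 2 × (1.960 + 0.842)² × (0.28/0.10)² = 123.1, rounded up to 124. At 124 per group the power is 80.3%. The stated figure is correct, and it belongs to gait speed alone.

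**2. Set objective, outcome and sizing side by side.**

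| Element | Content | Strength included? |
|---|---|---|
| Primary objective | Functional outcomes at 3 months and 1 year | No |
| Sample size | Gait speed, 0.10 m/s | No |
| Primary outcome | 10 MW, 8UG, isometric strength | Yes |
| Significance rule | P < 0.05 for all measures, unranked | Applies equally |

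Only the primary-outcome definition brings strength in, and nothing else in the article limits what a strength result may be used to claim.

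**3. Count the strength measures.** 3 (trunk) + 3 (operated hip) + 2 (other hip) = 8. With 10 MW and 8UG this makes 10 measures at each visit, 8 of them strength.

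**4. Illustrate the size.** The article gives no strength effect and no correlations, so these are assumptions: 124 per group with no dropout, no effect on gait speed or 8UG, the same true effect d (in SD units) in all eight directions, equal correlation r between directions, one visit, and success if any one direction is significant. The upper value of d borrows the gait-speed ratio, 0.10/0.28 = 0.357; the lower value, 0.20, is a smaller effect chosen for comparison.

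Each test statistic has mean d/√(2/124): 0.357/0.127 = 2.81 and 0.20/0.127 = 1.57. The critical value is 1.97. Simulating eight equicorrelated statistics (200,000 draws) gives the chance of at least one significant strength result:

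| True effect in all eight | r = 0.5 | r = 0.7 | r = 0.9 |
|---|---|---|---|
| 0.357 SD | 99% | 96% | 91% |
| 0.20 SD | 77% | 66–67% | 52% |

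If only one direction truly improves by 0.20 SD, the chance of at least one significant result favouring the intervention is about 35% to 37% (r = 0.7 to 0.5).

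These figures are power to detect a real strength gain. They do not measure how likely such a gain is to be misreported as function.

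**5. Check the remedy against N.** With 10 MW gait speed as the single primary measure, step 1 applies unchanged: 124 per group, 80.3% power.

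**The case against.** **Only one section defines the primary outcome.** A reader might infer that the abstract, Study design and Discussion offer a rival definition under which strength could not produce a primary success. They do not. The first two list what physiotherapists assess; the third says what the authors expect to improve. None assigns primary or secondary status. This objection stands: those passages show inconsistent terminology that should be reconciled, and no more.

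**Overlap between training and test.** A reader might also infer that part of any strength gain is practice of the tested task, because the home isometric sets say "every repetition will be made with the maximal voluntary effort exerted for 6 s" and the test says "a maximal voluntary isometric contraction for 6 s is used". Duration and effort match, but the home exercises are a sitting ball squeeze, a seated band abduction and a diagonal ball push, while the test is done standing on a dynamometer rig. All patients, controls included, also receive isometric strengthening in hospital. Carry-over is possible but the documents do not show it, and the point does not need it.

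**The percentages rest on assumptions.** The protocol states no any-one-of-eight rule and no strength effect. This stands, which is why the figures are given only as an illustration.

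**Strength is a defensible primary measure in a strength-training trial.** The Background links strength deficits to poor physical function. That supports measuring strength and studying it as a mechanism. It does not make it a functional outcome, and the objective as worded is functional.

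**The rule could sit in an unseen analysis plan.** A detailed decision rule could. But the article positively fixes strength as primary, and an analysis plan would inherit that.

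**Conclusion.** The point holds as a mismatch between primary outcome and primary objective. With strength primary, function as the objective, gait speed as the only basis for N, and every measure tested at 0.05 unranked, nothing in the article prevents a strength-only difference from being reported as primary efficacy. It does not say that this would be done.

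The size cannot be fixed from the documents. Under the stated assumptions, a true gain of 0.20 to 0.36 SD in all eight directions would give at least one significant strength result at one visit in roughly 50% to 99% of trials, and less often if only one direction improved. The mismatch itself depends on none of these assumptions. No stated figure is wrong. The change is worth making because it is cheap and protects the main claim.

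**What to change.** In Outcome measures:

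- Rest the primary claim on function, with gait speed on the 10 MW (the basis of the sample size) as the primary measure and 8UG as a supporting functional test.
- Report isometric strength as a secondary or mechanistic outcome.
- State that a strength difference without a functional difference does not support the primary claim.
- Use the term physical tests in one sense throughout the abstract, Study design, Outcome measures and Discussion.

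Trial status reports that recruitment began in 2018 and was continuing at submission, so this changes a stated primary outcome in a running trial. Record it as a dated amendment made before any between-group data are examined, and therefore before the interim analysis planned for the end of recruitment.

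**Cost.** No new data and no change in N. A strength-only benefit could be reported only as secondary. The change does not settle which of the two visits named in the objective carries the primary claim; that needs its own statement.

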#### Sample size calculation

A power calculation was performed based on a clinically significant difference in gait speed of 0.10 m/s on the 4- or 10-m walk (10 MW) test using data from Perera et al. [32]. Based on a substantial meaningful change of 0.10 m/s between the interventional and control groups and standard deviation of 0.28 m/s, with a significance level of 5% and a power of 80%, a needed sample size of 124 patients in each group was estimated (248 patients in total). All patients from surgeons, participating in the study, will be assessed for eligibility. A total of 124 patients in each hospital will be randomized according to the procedure described above on a 1:1 ratio, so that there will be 62 patients in group A and group B in both hospitals.

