Before any statistical analysis, data will be tested for normal distribution using the Kolmogorov–Smirnov test (K–S test). With normally distributed variables, the analysis of variance for repeated measures (AnovaRM) with two factors (time × group) will be employed. It will test the differences in the effects of two different exercise protocols. AnovaRM will be used to analyze between-group differences in the score changes among all time points, represented by preoperative measurements (on admission to the hospital) and measurements 1, 3, and 12 months postoperatively. Afterwards, the initial AnovaRM, post hoc tests with AnovaRM (time × group) with two time points will be performed. Differences between all pairs of time points will be analyzed. Additionally, the paired samples *t*-test to test for in-group differences in the score changes between the pairs of time points and the independent samples *t*-test for between-group comparisons at the same time point will be calculated. The bivariate Pearson correlation will be calculated for testing the relationships between variables representing relative changes in the results between two different time points (e.g., post-treatment/baseline) for each group separately. To test the reliability of maximal voluntary isometric contraction measurements and the 8UG test, we will use the intraclass correlation coefficient (ICC) with the two-way mixed-effects model with absolute agreement. Data will be presented as the arithmetic mean and standard deviation. In the case of a non-normal distribution, data will be presented as the median and interquartile range, and nonparametric tests will be used respectively for comparisons of dependent and independent groups. Instead of AnovaRM, the nonparametric marginal model (nparLD, R-statistics) [47] will be used. T-tests for dependent and independent samples will be changed with Wilcoxon matched-pair signed-rank test and Mann–Whitney *U* test, respectively. The Pearson correlation will be substituted with the Spearman rank correlation. Adverse effects comparison among the two groups will be made by using the chi-square test. We will consider a *P* value less than 0.05 as significant for all measures and use a 95% confidence interval (CI). A significance level (alpha) of 0.05 will be tested with a two-tailed test.

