### Data monitoring

Instead of a data monitoring committee (DMC), the presented study is supervised by a doctoral thesis review committee. It is composed of 3 members, whose names are available on request. The corresponding author is obliged to present the study design to the panel before starting the enrollment and to present the interim results and finally conclusions of the study. An interim analysis will be made after the completion of the patient recruitment, at which time the results will also be presented to the panel and any adverse effects recorded will be discussed. Given the existing data from the previous studies, we do not expect any major side effects requiring discontinuation of the study, except that it may be necessary to discontinue the protocol in individual patients.

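### The primary outcome is three physical tests (up to ten measures) at two visits, each tested at two-sided 0.05 with no lead endpoint, order or adjustment, while the sample size supports one gait-speed comparison.

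*Protocol article*

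**What the plan says.** - **Primary outcome** (Outcome measures): efficacy as measured by physical tests. "These comprise the 10 MW test, the 8-foot Up and Go (8UG) test, and isometric muscle strength". None is put first, and no composite or rule for combining them is given.
- **Strength** (Maximal voluntary isometric contractions): six directions are listed for the trunk and the side operated on, "Movement is assessed in 3 planes for the trunk (extension, left and right abduction) and operated hip (flexion, extension, and abduction". Two further directions, extension and abduction, are listed for the other hip, which makes eight. No summary strength score is named.
- **Time points** (Objectives): the primary objective asks whether "it can improve patient functional outcomes at 3 months and 1 year following surgery".
- **Tests** (Data management and analysis): a time-by-group repeated-measures ANOVA over four visits, then post hoc versions on two visits at a time, of which the plan says "Differences between all pairs of time points will be analyzed". Independent-samples t-tests between groups at the same time point are added, and are not made conditional on the ANOVA.
- **Threshold** (same section): a P "value less than 0.05 as significant for all measures", two-tailed.
- **Sample size** (Sample size calculation): "A power calculation was performed based on a clinically significant difference in gait speed of 0.10 m/s", with SD 0.28 m/s, 5% significance and 80% power, giving 124 per group.

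**The concern.** A 5% error rate belongs to one test, or to a set of tests governed by a rule. Here several measures at two visits each carry the full 5%, and any one of them could be presented as the trial's primary result. The measure and visit to rely on could be chosen after the results are known. The stated aim is a standardised programme for all THA patients in the country, and one favourable comparison picked from many would support that weakly.

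The sample size section treats the trial as having one gait-speed comparison. The outcome section does not. The two need to agree.

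**Working it through.** **1. The plan's own figure.** Inputs from Sample size calculation: difference 0.10 m/s, SD 0.28 m/s, two-sided 5%, 80% power, 1:1 allocation.

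n per arm = 2 × (1.960 + 0.842)² × 0.28² / 0.10² = 123.1, rounded up to **124**. Power at 124 per arm is 80.3%. The stated figure is reproduced, and it holds for a single comparison at 5%.

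**2. Counting the primary comparisons.**
- Named tests: 10 MW, 8UG and strength = 3. At two visits: 3 × 2 = 6 comparisons.
- With each strength direction counted: 3 (trunk) + 3 (operated hip) + 2 (contralateral hip) = 8, plus 10 MW and 8UG = 10. At two visits: 10 × 2 = 20 comparisons.

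**3. Chance of at least one false positive if the tests are independent.** For k two-sided tests at 0.05 the chance is 1 − 0.95^k. For results favouring the programme only it is 1 − 0.975^k.
- k = 6: 1 − 0.95⁶ = 26.5%; favouring the programme, 1 − 0.975⁶ = 14.1%.
- k = 20: 1 − 0.95²⁰ = 64.2%; favouring the programme, 1 − 0.975²⁰ = 39.7%.

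**4. With correlation.** The article gives no correlations between measures or visits, so these are assumed. The figures come from simulated correlated normal test statistics, with equal correlation among measures and between the two visits.

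| Correlation: measures / visits | 3 tests, either direction | 3 tests, favouring programme | 10 measures, either direction | 10 measures, favouring programme |
|---|---|---|---|---|
| 0 / 0 | 26% | 14% | 64% | 40% |
| 0.5 / 0.6 | 21% | 11% | 45% | 23% |
| 0.7 / 0.7 | 18% | 9% | 33% | 16% |
| 0.8 / 0.8 | 15% | 7% | 25% | 13% |

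The nominal values are 5% in either direction and 2.5% in favour of the programme.

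**5. What adjustment would cost if every comparison stayed primary.** Under Bonferroni over 20 comparisons (0.05 / 20 = 0.0025 each), power for the 0.10 m/s difference at 124 per arm falls to 41.6%, and 235 per arm would be needed for 80%. Over ten measures at one visit (0.005 each) power is 50.2%, and 209 per arm would be needed.

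**The case against.** **Ten measures is an inference.** The outcome section names three items. The strength section says how strength is measured and does not call each direction a primary endpoint; a summary score could sit in a fuller document. This stands. The three-test figure is the one that follows from the text, and the ten-measure figure is an upper reading.

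**Not every false positive would be claimed as efficacy.** Some would favour control. This also stands, and is why both counts are shown. A reader might infer that an ineffective programme has about an even chance of a primary success. The documents do not support that: it needs all ten measures, low to moderate correlation, and harmful results counted as successes.

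**The lead analysis is one time-by-group test per measure, and the rest is post hoc.** Counting only that test, the either-direction error is 14% for three independent measures and 40% for ten. At correlation 0.5 between measures it is about 13% and 30%; at 0.7, about 11% and 22%. That lowers the figure without bringing it to 5%. The t-tests are also added without being gated by it.

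**Larger figures are tempting.** Counting every pairwise post hoc test as a route to a primary claim would give a much higher rate, but the plan itself labels those tests post hoc. The interim look ("An interim analysis will be made after the completion of the patient recruitment") might be read as a second chance at significance. The Data monitoring section describes a presentation to the thesis committee and a discussion of adverse effects. It gives no efficacy threshold and no provision to claim success, so no inflation should be attached to it.

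**An article leaves detail to an SAP.** That would excuse silence. Here the article states both a multi-test primary outcome and an unadjusted threshold for all measures.

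**Conclusion.** The point holds. As written, the primary question is not tested at 5%. Over assumed correlations from 0 to 0.8, the chance of at least one false-positive primary comparison is about 15% to 26% for the three named tests at two visits, and about 25% to 64% if each strength direction counts. In favour of the programme alone, the ranges are about 7% to 14% and 13% to 40%. The ranges rest on the assumed correlations and on how strength is summarised, neither of which the article gives. The lowest of these figures is still about three times nominal. The sample size arithmetic is correct and is not in question; it simply covers one comparison.

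**What to change.** By a dated amendment, made before any between-group results are seen and therefore before the interim presentation:

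1. Name the between-group difference in 10 MW gait speed at 3 months as the single primary endpoint, two-sided 0.05. It is the measure behind the sample size, and the Discussion expects the largest differences at 3 months. 124 per arm keeps 80.3% power for it, before any loss to follow-up.
2. Test the next comparisons in a pre-stated order, each only if the one before succeeds: 10 MW at 12 months, then 8UG, then one strength measure or summary score. The investigators should choose the strength measure, and the visit for 8UG and strength, in advance.
3. Report all other measures, visits and pairwise tests with confidence intervals and no confirmatory claim.
4. Make no efficacy claim from the interim report.

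No new data or patients are needed. The cost is that 8UG, strength and the 1-year comparison lose stand-alone primary status, the last even though the primary objective names 1 year; the objective should be reworded to match. Recruitment was under way when the article was submitted, so the amendment must give its reasons and state that between-group results had not been seen. The registry entry must be updated.
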